## Abstract

**Introduction:**

Owing to increasing numbers of decompressive craniectomies in patients with malignant middle cerebral artery infarction, cranioplastic surgery becomes more relevant. However, the current literature mainly consists of retrospective single-centre (evidence class III) studies. This leads to a wide variability of technical approaches and clinical outcomes. To improve our knowledge about the key elements of cranioplasty, which may help optimising clinical treatment and long-term outcome, a prospective multicentre registry across Germany, Austria and Switzerland will be established.

**Methods:**

All patients undergoing cranioplastic surgery in participating centres will be invited to join the registry. Technical methods, materials, medical history, adverse events and clinical outcome measures, including modified Rankin scale and EQ-5D, will be assessed at several time points. Patients will be accessible to inclusion either at initial decompressive surgery or when cranioplasty is planned. Scheduled monitoring will be carried out at time of inclusion and subsequently at time of discharge, if any readmission is necessary, and at follow-up presentation. Cosmetic results and patient satisfaction will also be assessed. Collected data will be managed and statistically analysed by an independent biometric institute. The primary endpoint will be mortality, need for operative revision and neurological status at 3 months following cranioplasty.

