### Case report form

The specially designed and developed questionnaire (CRF) consists of four different parts (figure 1).

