**Figure 1 BMJOPEN2015009273F1:**
[figure not shown]
Study protocol of the German Cranial Reconstruction Registry (GCRR): using a structured questionnaire (for physicians and patients), patients’ clinical pathways will be monitored in four steps, from the craniectomy, over the cranioplasty and up to the long-term follow-up.

*Craniectomy*: The first part of the CRF covers the initial surgery, craniectomy. In addition to patient data (sex, age) and diagnosis, the initial neurological status (Glasgow Coma Scale (GCS), National Institute of Health Stroke Scale (NIHSS), World Federation of Neurosurgical Societies Scale (WFNS), Hunt and Hess), medical history (American Society of Anesthesiologists (ASA) Physical Status Classification), comorbidities (eg, diabetes, arterial hypertension, coagulopathy) and risk factors (eg, smoking status, drugs), is recorded. In addition, surgical data such as localisation of skin incision, trephination size and localisation, dura opening and closure technique (duraplasty) as well as materials used (eg, suture material and technique, drainage), are registered. Moreover, the experience of the surgeon, duration of operation, amount of blood loss and any perioperative antibiotic therapy given, will be documented. Finally, the storage of the bone and perioperative complications are listed. The initial observation period following DC (part 1) will end with discharge of the patient, where neurological status is recorded (Glasgow Outcome Scale (GOS), modified Ranking Scale (mRS), NIHSS).

*Cranioplasty*: The second part of the CRF covers all particular details of CP. Here, new patients can be included independently of the prior procedure, for example, when operated earlier at another institution. Again, preoperative data and the current neurological status are recorded. Particular attention is paid to the size of craniotomy and the type of CP (autologous vs alloplastic). All types of materials are included (eg, plastic, ceramic, titanium alloy, etc) and will be distinguished between patient-specific and hand-made CP. Details for fitting and fixating the material, simultaneous implantation of a CSF-shunt as well as standard parameters (suture material, size and number of drainage apparatus, perioperative antibiotics) will be covered. Similar to during the DC procedure, operating duration and amount of blood loss will be captured.

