*Postoperative monitoring*: The third part addresses all questions of the clinical follow-up at time of discharge. Acute complications such as bleeding events, seizures, wound healing disorders, infections and CSF fistulas, will be recorded. Removal of drains and control images are documented as well if surgical revisions or intensive care surveillance and/or treatment have been required in case of any complications. On discharge, neurological status will be recorded (GOS, mRs) again. This CRF can be used for any readmission due to complications or further surgical treatment as well.

*Follow-up*: Long-term clinical outcome after 12 months will be recorded; this will be continued annually, and is covered by a fourth part. Here, long-term complications such as aseptic bone necrosis, loosening or displacement of CP, wound healing disorders and revision procedures, if required, are recorded. Similar to in the earlier step, neurological status (GOS, mRs), patient satisfaction (SF12, EQ-5D) and cosmetic result will be assessed.

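### The abstract's primary endpoint includes neurological status at 3 months after cranioplasty, but the assessment schedule in the Methods names no assessment at 3 months

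*Protocol article*

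**What the plan says.** The primary endpoint appears only in the abstract, under Methods: "The primary endpoint will be mortality, need for operative revision and neurological status at 3 months following cranioplasty". The same paragraph places monitoring at inclusion and then "at time of discharge, if any readmission is necessary, and at follow-up presentation". No date is attached to the follow-up presentation.

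The main Methods give the schedule under Case report form: "The specially designed and developed questionnaire (CRF) consists of four different parts". The Figure 1 legend says that patients "will be monitored in four steps, from the craniectomy, over the cranioplasty and up to the long-term follow-up". The parts are then described one by one:

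- **Part 1, craniectomy:** runs from the initial operation to discharge after it.
- **Part 2, cranioplasty:** operative details, with neurological status before the operation.
- **Part 3, postoperative monitoring:** "The third part addresses all questions of the clinical follow-up at time of discharge". "On discharge, neurological status will be recorded (GOS, mRs) again". On re-use: "This CRF can be used for any readmission due to complications or further surgical treatment as well".
- **Part 4, follow-up:** "Long-term clinical outcome after 12 months will be recorded; this will be continued annually, and is covered by a fourth part". GOS and mRS are among its items.

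The Statistics section plans multiple imputation for missing values, with a complete-case sensitivity analysis.

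**The concern.** One of the three components of the primary endpoint is tied to a time at which the described schedule names no measurement. A centre that follows the form as described would assess a patient at discharge and, if nothing brings the patient back, not again until 12 months.

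The three components are affected differently. Death and operative revision are events: if their dates are recorded on a readmission or 12-month form, their status at 3 months can be worked out afterwards. Functional status on the mRS or GOS is a state at a point in time. If nobody assesses it near 3 months, it is lost.

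Functional status also belongs to the registry's first aim, stated at the end of the Introduction. Without a 3-month value, the analyst has three poor choices:

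- use the few values that readmissions happen to supply;
- impute almost the whole variable;
- substitute the discharge or 12-month value, which changes the time point being estimated without a planned decision to do so.

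**Working it through.** The plan gives no figure to reproduce on this point. The check sets the endpoint's time beside every neurological assessment that the text places after cranioplasty.

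| Source in the protocol article | Time after cranioplasty | GOS/mRS | Who is assessed |
|---|---|---|---|
| Abstract, primary endpoint | 3 months | required (scale not named) | all cranioplasty patients |
| CRF Part 3 | discharge | yes | all |
| CRF Part 3, re-used | at readmission | form available | only those readmitted |
| CRF Part 4 | 12 months, then yearly | yes | all still followed |
| Abstract, follow-up presentation | undated | not stated | not stated |

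**Step 1. Count.** Scheduled assessments named at 3 months: 0. Counting the 12 months from cranioplasty (the text does not give the starting point), the first dated visit after discharge comes 12 − 3 = 9 months after the endpoint's time.

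**Step 2. Can the undated item fill the gap?** The only text that dates follow-up is the description of Part 4, which begins at 12 months. The Figure 1 legend names the same pathway in four steps, ending in long-term follow-up, and mentions no 3-month step.

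**Step 3. Which components can be recovered?**
- Mortality by 3 months: yes, if the date of death is recorded.
- Revision by 3 months: yes, if the date of revision is recorded.
- Neurological status at 3 months: no. Discharge and 12-month values do not determine the value in between, because patients may improve or deteriorate at different rates.

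**Step 4. Does the missing-data plan help?** Multiple imputation needs enough observed values to learn how the missing variable relates to the others. Here the 3-month value would be missing by design for nearly all patients. The exceptions would be those readmitted near 3 months for complications or further surgery, whose functional status need not resemble that of the rest. Carrying their relationships over to everyone else rests on an assumption that the data cannot test. The complete-case sensitivity analysis would consist of the same small, selected group.

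**The case against.** The strongest reply is that absence is being read from a condensed article. The CRF itself is not reproduced, Figure 1 is not shown, and the abstract lists an undated follow-up presentation in the same paragraph as the 3-month endpoint. The description of Part 4 dates the long-term outcome at 12 months but does not expressly exclude an earlier visit. This stands as a limit on certainty: the documents support the statement that no 3-month assessment is named, and not that none exists. It does not remove the conflict. The article does not leave the schedule to another document; it sets it out part by part and gives follow-up a first date of 12 months. If the figure or the CRF does contain a 3-month visit, the Methods text still needs correcting.

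A second reply is that the study is purely observational, its endpoints are evaluated descriptively, and no sample size or test in the article depends on the 3-month value. That is true and limits the consequences. Even so, a descriptive primary endpoint has to be measured at its stated time.

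A reader might also try to put a number on the loss. The Introduction says that one-third of cranioplasty patients have complications, and Data management expects at least 80 patients per year, so 80 × (1 − 1/3) ≈ 53 per year might be inferred as the minimum without a 3-month value. The documents do not support this:

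- A complication rate is not a readmission rate. Complications during the index stay need no readmission.
- Part 3 also covers readmission for further surgical treatment, so readmissions are not capped at one-third.
- The 80 per year are registry inclusions, and patients may enter at craniectomy, so 80 is not a count of cranioplasties.

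**Conclusion.** The point holds as a contradiction within the article. The abstract fixes neurological status at 3 months after cranioplasty as part of the primary endpoint, and the schedule in the Methods names zero scheduled assessments at that time. No numerical estimate of the shortfall can be given from the documents, and none is needed.

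The conclusion is confined to the neurological component. Mortality and revision at 3 months remain obtainable, on the assumption that event dates are recorded, which the article does not state. The conclusion also assumes that the Part 4 description gives the true first date of routine follow-up.

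A reader might infer that any way round the gap biases the primary result. That is too broad. Relying on readmission-driven values is a selection problem, whereas substituting the discharge or 12-month value answers a question about a different time. Neither delivers the endpoint as stated.

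**What to change.** Reconcile the endpoint and the schedule in one of two ways.

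**(a) Collect the 3-month value.** Add a contact 3 months after cranioplasty for every cranioplasty patient, with a window stated in advance. Use the existing Part 3 items and record vital status, any revision with its date, mRS and GOS. Telephone contact can be allowed. An assessment made during a readmission counts only if it falls inside the window. The cost is one short contact per patient. It works only prospectively: a patient who passes the window unassessed cannot be recovered.

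**(b) Move only the neurological component.** Keep mortality and revision at 3 months, derived from recorded event dates, and place neurological status at the existing 12-month visit, counted from cranioplasty. This needs no new visit, but it is a formal amendment of the primary endpoint. Its price is a later readout and more loss to follow-up, which the article already lists as a limitation of its long observation period.

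Under either option, state the primary endpoint in the main Methods as well as in the abstract, name the scale that defines neurological status, give the follow-up presentation a date, and confirm that the form records dates of death and revision. These are text changes, plus a check of the CRF.

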**Ethics and dissemination:**

Ethics approval was obtained at all participating centres. The registry will provide reliable prospective evidence on surgical techniques, used materials, adverse events and functional outcome, to optimise patient treatment. We expect this study to give new insights in the treatment of skull defects and to provide a basis for future evidence-based therapy regarding cranioplastic surgery.

**Trial registration number:**

This trial is indexed in the German Clinical Trials Register (DRKS-ID: DRKS00007931). The Universal Trial Number (UTN) is U1111-1168-7425.

Strengths and limitations of this studyThe German Cranial Reconstruction Registry (GCRR) is a prospectively conducted, multicentre, international, open registry study in which patients will be observed long term.Owing to the prospective international nature (Germany, Austria, Switzerland), a very wide range of cranioplastic treatment options will be detected. Similar publications and studies are only monocentric.The registry includes patients with decompressive craniectomies in a wide range of acute diseases (eg, traumatic brain injuries, space-occupying cerebral infarction, subarachnoid and intracerebral haemorrhage, etc) as well as destructive or osteolytic bone tumours.A limitation of the study is that the GCRR is not a randomised study, but only a pure observational study. Specific treatment strategies will not be compared against each other.One of the strengths as well as simultaneous limitation of this study is the planned long observation period of up to 10 years. There is the possibility of a high number of participants lost to follow-up.

## Introduction

Several prospective clinical trials have demonstrated that early decompressive craniectomy (DC) increases survival in patients with space-occupying middle cerebral artery (MCA) infarction by reducing intracranial pressure. Subsequently, numbers of DCs are continuously rising.^1–5^ Large cerebral infarctions cause space-occupying brain oedema, which is considered the main reason for a mortality rate of up to 80%.^6–8^ Despite best conservative treatment, outcome was generally poor before establishing DC as an early treatment option.^6^ Recently, analyses of prospective randomised clinical trials including the DECIMAL (Decompressive Craniectomy In Malignant MCA Infarction), HAMLET (Hemicraniectomy After Middle cerebral artery infarction with Life-threatening Edema Trial), DESTINY I and DESTINY II (Decompressive Surgery for the Treatment of malignant Infarction of the middle cerebral artery) trials, and a prospective pooled data analysis of the first three trials mentioned above, proved the benefit for patients with malignant MCA infarction.^2–4^
^9–11^ The probability of survival for patients aged 60 years and younger increases up to 80% following DC (vs 28% without DC) and the probability of survival with a modified Rankin scale (mRS) of ≤3 doubles.^2^ Based on these beneficial experiences, DC procedures have also been proposed as a therapeutic option in refractory intracranial hypertension or malignant brain oedema due to traumatic brain injury (TBI), acute subdural haematoma, subarachnoidal haemorrhage or encephalitis.^12–17^

Each successful DC requires a secondary operative procedure: cranioplasty (CP). Besides refitting the integrity of the skull, protecting the brain and restoring the cosmetic aspect, CPs have gained a major focus in the rehabilitation process. CPs may also improve the neurological condition of patients with a so-called ‘sinking skin flap syndrome’, and associated deteriorations, dramatically.^18^ Furthermore, CP may play an important role in reconstruction procedures following excision of primary osseous tumours, meningiomas infiltrating the bone and simple removal of bone flaps following postoperative infection.

Both DC and CP are performed with increasing frequency, while published series reveal a 20–50% complication rate. Complications following DC after malignant infarction include haematomas, meningitis, seizures and wound infections.^19^ Major complications of DC after severe TBI are herniation of the brain tissue through defects (34%), subdural effusions (54%) and hydrocephalus (14%).^20^ One-third of all patients undergoing CP suffer from complications,^21–23^ of which wound infections and wound healing disorders, in up to 25% of patients, are of major importance, as is aseptic bone necrosis, in up to 18%.^21^
^24^ Although some predictors, such as multiple fractures within the bone flap, wound infection after CP and insecure fixation of the bone, may increase bone resorption rates, the impact of other factors, such as bone flap preservation or timing of CP, is unknown.^21^
^25^ In the absence of prospective clinical studies, and based on numerous retrospective monocentre studies alone, one cannot reach consensus regarding timing of CPs, materials and perioperative management.^21^
^23^
^26–29^

The aims of this international prospective multicentre register are to (1) identify surgical and medical factors with a strong influence on patient's outcome and functional status, and (2) establish an evidence-based therapeutic approach optimising timing and the procedures themselves, thus minimising perioperative and postoperative complication rates and improving clinical outcome in this group of patients.

## Methods

### Study design

The German Cranial Reconstruction Registry (GCRR) is a prospectively conducted, multicentre, open registry, in which patients will be observed long term. The study is a procedure-specific registry, initiated by a consortium of individual members of the Section for Neurotrauma and Intensive Care in Neurosurgery of the Deutsche Gesellschaft für Neurochirurgie (DGNC). A total of 10 German neurosurgical departments have constituted a Steering Committee, which will be responsible for the scientific goals of the registry and guarantee the independence of the data analysis performed by a biometric institute. In 2014, organisation and goals of the registry as well as the implementation of the GCRR were determined. Neurosurgical units in Germany, Austria and Switzerland conducting DC and CPs are invited to join the registry and to recruit patients.

### Study setting and type of participants

All patients undergoing CP are included in the study. Inclusion criteria are all clinical conditions that require a temporary removal of the skull, for example: TBIs, space-occupying cerebral infarction and subarachnoid haemorrhage as well as destructive or osteolytic bone tumours. Patients undergoing craniectomy without CP (eg, suboccipital), craniosynostosis repair or skull base approaches with complex reconstruction, will not be included (table 1). Patients can be included at two time points: either at the initial event of DC or at readmission for CP.

**Table 1 BMJOPEN2015009273TB1:** Inclusion and exclusion criteria for patients to participate or not in the GCRR

Inclusion criteria	Exclusion criteria
Patients with a clinical condition that requires *temporary* removal of the cranial bone (DC) Space-occupying cerebral infarction Traumatic brain injury Subarachnoid haemorrhage Intracranial haemorrhage Sinus venous thrombosis Space-occupying cerebral infections Patients after DC who now require surgical CP Patients with osteolytic or bone-destructing tumours of the skull Legal age (≥18 years)	Patients with a clinical condition that requires *permanent* removal of the cranial bone Patients in palliative care Patients with craniofacial malformations (eg, craniosynostosis) Patients who require skull base reconstruction Patients after suboccipital DC

CP, cranioplasty; DC, decompressive craniectomy; GCRR, German Cranial Reconstruction Registry.

### Informed consent

Written informed consent for this study will be obtained from the patient or the patient’s authorised representative prior to study inclusion. The study will be conducted in accordance with the provisions of the Declaration of Helsinki.

### Data collection

According to a standardised questionnaire for DC and CP, patient-specific data, risk factors, surgical details, materials for CP, and intraoperative and postoperative complications, will be recorded. Data acquisition will be paper-based (case report form, CRF), and patient-specific data will be anonymised by the study centre. The data will then be transferred to the Department of Medical Biometry Heidelberg (Institute of Medical Biometry and Informatics, IMBI) and transmitted into an electronic database. Despite anonymous data acquisition, patient tracking remains possible for analysing specific events such as clusters of complications or unexpected severe events.

### Case report form

The specially designed and developed questionnaire (CRF) consists of four different parts (figure 1).

**Figure 1 BMJOPEN2015009273F1:**
[figure not shown]
Study protocol of the German Cranial Reconstruction Registry (GCRR): using a structured questionnaire (for physicians and patients), patients’ clinical pathways will be monitored in four steps, from the craniectomy, over the cranioplasty and up to the long-term follow-up.

*Craniectomy*: The first part of the CRF covers the initial surgery, craniectomy. In addition to patient data (sex, age) and diagnosis, the initial neurological status (Glasgow Coma Scale (GCS), National Institute of Health Stroke Scale (NIHSS), World Federation of Neurosurgical Societies Scale (WFNS), Hunt and Hess), medical history (American Society of Anesthesiologists (ASA) Physical Status Classification), comorbidities (eg, diabetes, arterial hypertension, coagulopathy) and risk factors (eg, smoking status, drugs), is recorded. In addition, surgical data such as localisation of skin incision, trephination size and localisation, dura opening and closure technique (duraplasty) as well as materials used (eg, suture material and technique, drainage), are registered. Moreover, the experience of the surgeon, duration of operation, amount of blood loss and any perioperative antibiotic therapy given, will be documented. Finally, the storage of the bone and perioperative complications are listed. The initial observation period following DC (part 1) will end with discharge of the patient, where neurological status is recorded (Glasgow Outcome Scale (GOS), modified Ranking Scale (mRS), NIHSS).

*Cranioplasty*: The second part of the CRF covers all particular details of CP. Here, new patients can be included independently of the prior procedure, for example, when operated earlier at another institution. Again, preoperative data and the current neurological status are recorded. Particular attention is paid to the size of craniotomy and the type of CP (autologous vs alloplastic). All types of materials are included (eg, plastic, ceramic, titanium alloy, etc) and will be distinguished between patient-specific and hand-made CP. Details for fitting and fixating the material, simultaneous implantation of a CSF-shunt as well as standard parameters (suture material, size and number of drainage apparatus, perioperative antibiotics) will be covered. Similar to during the DC procedure, operating duration and amount of blood loss will be captured.

*Postoperative monitoring*: The third part addresses all questions of the clinical follow-up at time of discharge. Acute complications such as bleeding events, seizures, wound healing disorders, infections and CSF fistulas, will be recorded. Removal of drains and control images are documented as well if surgical revisions or intensive care surveillance and/or treatment have been required in case of any complications. On discharge, neurological status will be recorded (GOS, mRs) again. This CRF can be used for any readmission due to complications or further surgical treatment as well.

*Follow-up*: Long-term clinical outcome after 12 months will be recorded; this will be continued annually, and is covered by a fourth part. Here, long-term complications such as aseptic bone necrosis, loosening or displacement of CP, wound healing disorders and revision procedures, if required, are recorded. Similar to in the earlier step, neurological status (GOS, mRs), patient satisfaction (SF12, EQ-5D) and cosmetic result will be assessed.

